### Secondary outcome measures

3.2

•Postoperative pain (Postoperative pain levels will beassessed twice daily (BID) during the first three days postoperatively).•Drainage time in days (rounded to the nearest whole number).•Length of hospital stay in days (rounded to the nearest whole number).•Postoperative complications

These parameters will be collected as part of the clinical routine. Additional patient data will include the type of surgery (specific lobe), pre-disease profile, laboratory parameters, and pre- and postoperative radiological and clinical findings. The preoperative preparation, diagnostic procedures, and pre-admission process will follow the standard clinical routine without any deviations.

## Implementation

4

The physicians at the Center for Thoracic Diseases (CTD) will strictly follow the established clinical routine for surgery preparation, diagnostics, and pre-admission procedures. Informed consent will be obtained from all participating patients by the physicians. Patients who provide consent for surgery will be informed about the opportunity to participate in the study, provided they meet the inclusion criteria and have no exclusion criteria. During the consenting process the benefits and risks will be thouroughly explained, and enrollment will proceed after written consent has been obtained.

All referrals for surgery are discussed in the local multidisciplinary team meeting. The choice of the surgical approach is always determined by a board certified thoracic surgeon. All surgical procedures will be performed by or supervised by a board certified thoracic surgeon with experience in uniportal thoracoscopic lung resections (>100 thoracoscopic anatomic lung resections). Three consultant surgeons fulfill these criteria in our department. The treatment method implemented will be based on randomization, with one group receiving 14F drainage and the other group receiving 24F drainage. The consultant surgeon performing or supervising the procedure will be responsible for deciding if the patient is eligible for randomization. It is our institutional practice to ventilate the lung at the end of the procedure and perform an underwater air leak test in order rule out major air leaks and check the bronchial closure.

If the thoracic consultant considers the patient eligible for randomization, the randomization process will take place before insertion of the drain at the end of the procedure. The drains will be inserted through the surgical incision into the chest cavity, and their positioning will be visually confirmed before securing them to the skin using a suture made with Supramid 0 thread from B.Braun. Standardized sutures will be used to close the muscle, subcutaneous tissue, and skin. Both groups' drains will be connected to a digital thoracic drainage system (Thopaz from Medela Healthcare, Switzerland) with a suction of −8 cm H2O (physio mode). All electronic suction devices will be calibrated before use as recommended by the manufacturer.

Daily clinical data will be collected, including the fever curve to monitor body temperature, pain intensity using the Numerical Analog Scale (NAS) recorded twice daily, analgesic medication administered, quantity and quality of secretion per 24 h (recorded by nursing staff at 6 a.m.), and assessment of parenchymal fistula (recorded during the morning visit at 7:45 a.m. based on the graph displayed in the last 24 h). Incision wound checks will be performed on the day of surgery, at discharge, and during follow-up visits at the outpatient clinic, usually scheduled within 14 days after discharge.

Postoperative procedures, including drainage and pain management, will follow our standard operating procedure for postoperative care after thoracic surgery. Patients following anatomic lung resections are usually monitored for 24 h on a high dependency or intensive care unit. If the immediate postoperative period is uneventful the patients are usually transferred on the ward on the first postoperative day. The patients are usually discharged one day after drain removal. A final follow-up visit is part of our postoperative care standard operating procedure and usually takes place 2 weeks after surgery in the outplatient clinic.

As part of routine clinical practice, patients typically receive three peripheral nonsteroidal analgesics and a perivertebral pain catheter with 0.375 % Ropivacain at a rate of 10 ml/h. A chest X-ray (PA view) will be performed on the first postoperative day, immediately prior to drainage removal, and during follow-up visits at the outpatient clinic. If the X-ray shows any pathological findings, further tests may be requested as indicated.

Before discharge, patients are informed to visit the Department of Thoracic Surgery if they experience any complaints.

A risk-benefit analysis has determined that the placement of a postoperative chest drain is a routine procedure without additional burden to the patient. While treatment with a 24F chest drain is a standard procedure with no increased risk, treatment with a 14F chest drain may result in more postoperative interventions due to potential complications such as pneumothorax or drain occlusion. However, the medical staff at CTD is highly senzibilized to these possibilities and prepared to promptly react if such events occur. After the surgery, all patients are monitored on the intermediate care unit overnight under close supervision by the medical staff.

Patients in the experimental group may experience less pain, reduced morbidity, shorter hospital stays, and increased satisfaction.

### Drop-out

4.1

There are multiple factors that can result in the discontinuation of an individual's participation in the study, such as the participant's voluntary withdrawal or failure to meet the inclusion and/or meeting the exclusion criteria. However, it is important to note that these circumstances do not fall within the category of drop-outs, since no randomization takes place prior to these occurrences.

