### Study participants

2.1

A total of 40 patients undergoing uniportal video-assisted thoracoscopic lobectomy (uVATS) at the Center for Thoracic Diseases (CTD) will be recruited for this study. Patients meeting the inclusion criteria and providing informed consent will be enrolled. The sample size of 40 patients would allow us to analyze 20 patients on every group. This number is considered appropriate for Phase I trials in order to collect the necessary safety information and perform subsequent sample size calculations for a larger efficacy trial. In order to analyze 40 patients and taking into account the increasing number of anatomic segmentectomies performed and our conversion rate, we assume that around 100 patients need to be screened (Fig. 1).

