### Exclusion criteria

2.3

Patients who do not undergo lobectomy using minimally invasive techniques, and patients undergoing other types of lung resection (wedge resection, segmentectomy, bilobectomy/pneumonectomy) will be excluded. Patients with a history of congenital or acquired coagulopathy, use of direct oral anticoagulants, deviation from standard postoperative pain management regimen, or chronic analgesic therapy will also be excluded.

The study will randomize the 40 patients into two groups of equal size. Group 1 (control group) will consist of 20 patients who will receive a conventional 24 French (24F) chest drain according to current standards. In Group 2, a 14 French (14F) drain will be used (intervention group), which will be placed intraoperatively through the same access required for lung resection. The 14F drain will be secured to the skin with a separate suture, following the same technique as the placement of the 24F drain.

Drain removal is indicated by a board certified thoracic surgeon during the morning round on every postoperative day. In order for the drain to be removed there must not be any air leak during the past 24 h before the morning ward round and the fluid drainage has to be less than 5 ml/kg/24 h [14].

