### Data management and protection

4.4

The data collected will be stored digitally on data storage devices at the Thoracic Surgery department of the University Medicine Mainz. Data security will be ensured by following the data protection guidelines of the University Medical Center Mainz and complying with legal requirements, including the General Data Protection Regulation (GDPR).

The study will be conducted in accordance with the current version of the Declaration of Helsinki. The study protocol has been approved by the Ethics Committee of the district medical council of Rhineland-Palatinate (approval Nr. 2021–15994). All patient information, including names and other confidential data, will be treated with medical confidentiality and will be subject to the provisions of the State Data Protection Act of Rhineland-Palatinate and the Federal Data Protection Act (LDSG BW and BDSG). Patient data will only be shared in pseudonymized form, and original documents will not be accessible to third parties.

The data will be stored for a period of 25 years, in compliance with the provisions of the Good Clinical Practice (GCP) regulation of August 9, 2004. Participation in the study is voluntary, and patients have the right to withdraw their consent at any time without providing a reason and without any negative impact on their medical care. Before the study commences, participants will be provided with written and verbal information about the nature and scope of the planned investigation, including potential benefits and risks to their health. Their consent will be documented through the signing of an informed consent form. In the event of withdrawal from the study, any data already collected will be destroyed, or the patient will be asked for permission to analyze the existing materials.

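### Section 4.1 treats withdrawals and exclusions as always preceding randomisation, which sections 2.3, 4 and 4.4 contradict, so randomised patients and their outcome data can be lost uncounted

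*Protocol article*

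**What the plan says.** Section 4.1 (Drop-out) lists reasons for ending participation, "such as the participant's voluntary withdrawal or failure to meet the inclusion and/or meeting the exclusion criteria", and then states that "these circumstances do not fall within the category of drop-outs, since no randomization takes place prior to these occurrences".

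Four other places in the article bear on this:

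- Section 4 (Implementation): "the randomization process will take place before insertion of the drain at the end of the procedure". The same section places the final outpatient visit about two weeks after surgery.
- Section 4.4 (Data management and protection): "patients have the right to withdraw their consent at any time without providing a reason". On withdrawal, "any data already collected will be destroyed, or the patient will be asked for permission to analyze the existing materials".
- Section 2.3 (Exclusion criteria): patients with "deviation from standard postoperative pain management regimen, or chronic analgesic therapy will also be excluded".
- Section 2.1 (Study participants) sets screening at around 100 patients "In order to analyze 40 patients", 20 per group. Section 4.3 (Biometry) provides exactly 40 allocation sheets.

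**The concern.** Randomising late, at the end of surgery, is sensible: it removes conversions and changes of resection before they can become losses. It cannot prevent losses that come afterwards, and every primary and secondary outcome arises afterwards. Section 4.1 nevertheless gives the timing of randomisation as a general reason why withdrawal and exclusion are never drop-outs. Read literally, a patient who withdraws on the second postoperative day is not a drop-out.

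Section 4.4 adds to the problem. The same patient's data are either destroyed or kept with permission, and nothing says which course is taken or who decides. The choice could be made after the outcome is known. A primary-endpoint event could then leave the dataset with no trace in the count of losses.

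The drain-related complication rate is the primary outcome. It is also close to what the stopping rule in section 4.2 monitors, and it is the input for planning the later non-inferiority trial. With 20 patients per arm, single events matter.

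**Working it through.** **1. The passages side by side**

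| Circumstance named in 4.1 | 4.1 places it | Other sections |
|---|---|---|
| Voluntary withdrawal | before randomisation | 4.4 allows it at any time; section 4 randomises in theatre and follows patients for about two weeks |
| Meeting an exclusion criterion | before randomisation | 2.3 includes deviation from the postoperative pain regimen; an actual deviation occurs after surgery, hence after randomisation |

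Both halves of the rule fail, each on a different section. The withdrawal wording in 4.4 contradicts only the first half; the criterion in 2.3 contradicts the second.

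**2. The plan's own figure**

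20 + 20 = 40 analysed, from 40 sheets. The sum is right. Section 2.1 justifies 40 as suitable for a phase I trial and gives no error rate, effect or loss rate, so no power formula can reproduce it. The allowance for loss after randomisation is 40 − 40 = 0. With an assumed loss of 5% or 10%, 40 × 0.95 = 38 or 40 × 0.90 = 36 remain. To keep 40, one would randomise 40/0.95 = 42.1, so 43, or 40/0.90 = 44.4, so 45.

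**3. Effect of one deleted patient on an arm of 20** (event counts are illustrative)

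If the deleted patient had an event, x/20 becomes (x − 1)/19, a fall of (20 − x)/380.

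- x = 2: 2/20 = 10.0% (exact 95% CI 1.2 to 31.7) becomes 1/19 = 5.3% (0.1 to 26.0). The fall is 18/380 = 4.7 points.
- x = 3: 3/20 = 15.0% becomes 2/19 = 10.5%. The fall is 17/380 = 4.5 points.

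If the deleted patient had no event, x/20 becomes x/19, a rise of x/380. For x = 2 that is 2/380 = 0.5 points. So it matters far more which patient is lost than that one is lost.

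**4. Effect on the stopping rule**

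The rule acts when more than 20% of the first ten experimental patients are affected, that is, at 3 or more of 10. Suppose 3/10 are affected and one of the three is deleted:

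- If the denominator shrinks, 2/9 = 22.2%, and the rule still acts.
- If the place is taken by a patient without an event, 2/10 = 20.0%, and the rule does not act.

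The article does not say which of the two would apply.

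**The case against.** The best defence is that 4.1 was meant only for losses at screening and in theatre, where its reasoning is correct. But the section names withdrawal and exclusion without that limit, and it leaves no category for what happens later. Likewise, the pain-regimen criterion might be meant for a deviation foreseen before surgery; section 2.3 does not say so.

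A second defence is that few withdrawals are likely. Outcomes are collected in clinical routine, the follow-up visit is standard care, and little study burden remains once the drain is in. This stands as a reason to expect small numbers. It does not make the rule correct.

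A third is that analysis sets and sensitivity analyses usually belong in a full protocol or analysis plan that is not shown. That is fair, and their absence is not the point. The point is a stated rule that is wrong. The analysis changes are proposed only because correcting the rule makes them necessary.

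Three stronger readings are tempting, and the documents do not support them:

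- *Destruction is the default.* Section 4.4 names two alternatives and no default.
- *The 14F complication rate is biased downward.* That needs an event, a withdrawal and no permission in the same patient. Nothing in the article shows that this will happen, or that it would be confined to one arm.
- *One lost event removes over a third of the information.* The Discussion's 8.1% and 5.2% give 20 × 0.081 + 20 × 0.052 = 2.66 events, and 1/2.66 = 38%. But those are obstruction rates, not rates of this trial's composite endpoint, and a share of events is not a share of statistical information.

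**Conclusion.** The contradiction is certain and rests on the text alone: section 4.1 cannot stand beside sections 2.3, 4 and 4.4. Followed as written, withdrawal or exclusion after randomisation is not counted as a drop-out, and a withdrawn patient's outcome data survive only with permission.

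The size of the harm is conditional. If a deleted patient had an event, the observed rate in that arm is too low by about 4 to 5 percentage points, for example 10.0% shown as 5.3%. This assumes 20 patients in the arm, one such loss and the illustrative counts above. How often it would happen cannot be derived from the article. The reduction from 40 to 38 or 36 under assumed losses matters less, since 40 rests on convention rather than on power.

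The point should be corrected because data once destroyed cannot be recovered.

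**What to change.** - **Section 4.1:** state that withdrawal or exclusion after an envelope is opened is a post-randomisation loss, reported by arm with the reason where the patient gives one.
- **Sections 2.3 and 4.1:** reconcile the pain-regimen criterion with the drop-out rule, so that it does not remove randomised patients from the primary analysis. This concerns the analysis only, not how pain is treated.
- **Section 4.3:** analyse all randomised patients in the assigned group.
- **Section 4.4 and the consent form:** always ask for permission first, and keep data collected up to withdrawal unless the patient asks for deletion, as far as law and consent allow.
- **Reporting:** for any patient whose data were deleted, show the primary result with that patient counted as an event and as a non-event. With 1 event among 19 retained and one deleted, the range is 1/20 = 5.0% to 2/20 = 10.0%.

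The cost is a change of wording and notification of the ethics committee. The new data rule would apply only to patients who consent under the new wording; for those already enrolled, the existing consent governs, and the two-way display covers any deletion.

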### Safety

4.2

If the rate of complications or the need for renewed drainage of the pleural cavity in the experimental group exceeds 20 % among the first ten subjects, the study will be discontinued.

### Biometry

4.3

The collected measurement data will be described using descriptive statistics and compared with routine clinical data from both groups. The goal is to determine the number of cases in each group for a “non-inferiority” study to assess the risk of complications in the experimental group using a 14F chest tube.

This study is a prospective phase I trial that involves randomization of participants using an “envelope” randomization method. A third-party non-physician writes either 14 or 24 on 40 sheets, which are then placed in sealed envelopes. During the chest drain placement procedure, a random envelope is selected to determine the size of the chest drain.

The collected data will be analyzed using descriptive statistics initially. Subsequently, exploratory analyses will be conducted to compare groups and identify risk factors. Statistical methods such as t-tests, Mann-Whitney U-tests, analysis of variance, or Kruskal-Wallis tests will be used based on the sample size, scale level, and variance of the parameters. If necessary, multivariable test methods like logistic regression or multiple linear regression will be employed to assess the influence of multiple variables on an outcome variable.

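### Drawing any envelope in theatre leaves no allocation sequence to check, and a second draw would go undetected; numbered envelopes opened in order would close this gap.

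*Protocol article*

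**What the plan says.** Section 4.3 (Biometry) describes how the envelopes are made: "A third-party non-physician writes either 14 or 24 on 40 sheets, which are then placed in sealed envelopes". It then describes how they are used: "During the chest drain placement procedure, a random envelope is selected to determine the size of the chest drain". It says nothing on numbering, opacity, custody, a log of openings, or who makes the draw.

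Section 4 (Implementation) gives the setting. On the leak test it says: "It is our institutional practice to ventilate the lung at the end of the procedure and perform an underwater air leak test". On eligibility it says: "The consultant surgeon performing or supervising the procedure will be responsible for deciding if the patient is eligible for randomization". Randomization follows that decision and precedes insertion of the drain.

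Section 2.3 fixes the target split: "The study will randomize the 40 patients into two groups of equal size", with 20 patients in the control group. Section 2.1 agrees: "The sample size of 40 patients would allow us to analyze 20 patients on every group".

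**The concern.** An envelope system protects against selection only if each envelope belongs to one place in a fixed order, so that the envelope opened for a patient can be compared with the one that was due. When any envelope may be taken, that comparison cannot be made. If a first envelope were set aside and another opened, the procedure as described would leave no trace of it.

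This matters more here than in many trials. When the draw takes place, the team has completed the resection, probably knows the leak-test result, and has just judged the patient eligible. Drain size cannot be hidden from the person inserting it. Safety is the declared purpose of the trial, and its complication rates are meant to feed the sample size of a later non-inferiority trial. With 20 patients per arm, one or two steered allocations could colour both uses.

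**Working it through.** **The plan's own figure.** Sections 2.1 and 2.3 give 20 per group, and 20 + 20 = 40 agrees with the stated total. No power calculation underlies this number, so there is nothing further to reproduce.

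**What the stated method makes checkable.**
- Section 4.3: one envelope is picked at random from those available. Even if the envelopes carried numbers, the numbers would not set the order of opening.
- Section 4: eligibility is decided first, then the envelope is drawn, then the drain goes in.
- Together, these show who was judged eligible and which size was inserted, but not which size was due. Without that last item there is nothing to audit against.

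**Effect of one unrecorded redraw.** Assumption: 20 sheets of each size, which section 2.3 implies and section 4.3 does not state. For the first patient:
- One draw: P(preferred size) = 20/40 = 0.50.
- One redraw if the first is not the preferred size, with the first envelope left out: 1 − (20/40) × (19/39) = 1 − 380/1560 = 0.756.
- The same with the first envelope returned and mixed in: 1 − (20/40)² = 0.75.

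The result hardly depends on what happens to the first envelope.

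**Effect of one redirected patient.** Assumptions: 20 analysed per arm, the patient would have an event with either drain, and the patient who takes the vacated place has none. One arm loses an event (1/20 = 5 points) and the other gains one (1/20 = 5 points). The risk difference moves by 5 + 5 = 10 percentage points. This shows how sensitive the trial is; it does not estimate how often redirection would happen.

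**Predictability, to choose the remedy.** Someone who knows the past allocations and always guesses the size with more envelopes left is right, on average, m + (4^m / C(2m, m) − 1)/2 times out of 2m, where m is the number of each size in a block.
- One list of 20 and 20 (m = 20): 23.49 of 40, or 58.7%.
- Known blocks of 4 (m = 2): 2 + (16/6 − 1)/2 = 2.83 of 4, or 70.8%.
- Known blocks of 6 (m = 3): 3 + (64/20 − 1)/2 = 4.10 of 6, or 68.3%.

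A single shuffled list is therefore no more predictable than a pile of 20 and 20, and less predictable than short known blocks.

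**The case against.** The strongest reply is that a journal article condenses a fuller protocol, and that numbering, opacity, custody and logging belong in that fuller document. This stands as far as it goes. A reader might infer that the envelopes are unnumbered or see-through, or that envelopes are put back. The article says none of this, and its silence is not evidence. The reply does not reach the core, because picking an envelope at random is the stated method. A fuller document could add a log, but it could not require opening in sequence without contradicting section 4.3.

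Other objections stand and limit the point:
- **Concealment is not absent.** The envelopes are sealed and a third-party non-physician prepares them. The article does not say that the surgeon makes the draw.
- **Late randomization is not a fault.** Settling eligibility first limits exclusions after randomization and should be kept.
- **Unequal groups are not established.** A reader might take section 4.3 to mean that each sheet is written independently, in which case an exact 20:20 split would have probability only 0.125. Section 2.3 fixes equal groups and 40 envelopes are made, so 20 of each is the natural reading. That probability does not apply.
- **Motive and direction are not established.** A reader might infer that leaking patients would be steered to 24F, making 14F look safe. The background section reports a preference for larger drains among many surgeons in general, because of obstruction. It does not say this of the trial's three consultants, and the discussion section expects the small drain to cope with fluid and air leaks.
- **No expected event count can be given.** The obstruction rates cited in the discussion (8.1% and 5.2%) cover one component of a composite endpoint and are not rates for this operation.

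**Conclusion.** The point holds as a weakness in a stated design choice. The free pick provides no sequence against which an assignment can be verified, in a setting where the patient's intraoperative course is known and the drain size is visible. Concealment is partial and not secured.

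Two figures give the size. One undetected redraw takes the chance of a preferred size from 0.50 to 0.756, assuming 20 sheets of each size and the first patient. One redirected patient with an event moves the risk difference by 10 points, assuming 20 per arm, an event with either drain, and none in the patient who takes the vacated place. Both show what the procedure would allow. The documents do not support a claim that allocation will be subverted, that any bias would favour a particular drain, or that the groups will be unequal. The change should be made because it is cheap and because, without it, the safety comparison cannot be defended if its allocation is questioned.

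**What to change.** Replace the description of the draw in section 4.3 with the following:

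1. The third-party non-physician prepares a computer-shuffled list of exactly 20 allocations to 14F and 20 to 24F, matching section 2.3, and keeps it away from the surgical team.
2. The allocations go into sequentially numbered, opaque, sealed envelopes.
3. The consultant's eligibility decision is recorded before any envelope is opened. This keeps the order already in section 4 and adds the written record.
4. Envelopes are opened strictly in number order. Patient ID, date and time are written on the envelope before opening.
5. All envelopes, used and unused, are kept and reconciled against the list at the end of the trial.

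The cost is about an hour of preparation and a log sheet. The total of 40 and the time of randomization do not change. Permuted blocks are not required: a single-centre, unstratified trial reaches 20:20 without them once all 40 envelopes are used, and short blocks would make allocations easier to guess for a team that sees each drain.
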